For the measurement of the primary outcome, a physician or nurse, blinded to treatment allocation, will assess temperature, respiratory rate, and evident increased work of breathing, in person using standardized protocols; these physical examination findings are the most important when assessing response to therapy. Lack of fever at home will be verified through assessment of the symptom diaries. Medical visits for persistent respiratory illness will be assessed by directly asking the participant’s caregiver; though caregiver report is not an entirely reliable modality, we believe that the sensitivity and specificity of the question “Did your child see another health professional because of a concern about respiratory illness within the past ten days?” should be adequate.

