#### Follow up

The RA will phone the caregiver once at day 3–5 and once at day 7–10 to verify the clinical stability of the participant. Caregivers will also be explicitly informed that they can contact the study team in the event of a concern prior to the scheduled phone calls. The caregiver will be given a study diary to complete each day, which will include the following: temperature, dyspnoea (older participants), increased work of breathing, school attendance, caregiver absenteeism from work duties, days of mild diarrhoea, mild (abdominal discomfort, rash) and severe (anaphylaxis) drug adverse reactions, and the number of missed medication doses, if applicable. The caregivers will be instructed how to take their child’s temperature and assess increased work of breathing. Any participant who has persistent fever more than 3 days post-enrolment will receive an additional 5 days of open-label amoxicillin after the initial 5 days (i.e. will receive a guaranteed 10 days of antimicrobial agents). Any participant who worsens clinically subsequent to enrolment at any time point prior to the primary outcome visit will be urged to seek medical care without delay either at the site where recruitment took place or with another physician (e.g. family physician, walk-in clinic); all participants will be provided with printed documentation about the SAFER trial and contact information for the local Principal Investigator (PI) for the benefit of the medical professional re-evaluating the participant. The criteria for permanent discontinuation of the experimental aspect of the study protocol in an individual subject are as follows: failure to defervesce by day 4 post-enrolment; requirement for hospitalization because of worsening respiratory illness; severe reaction potentially associated with amoxicillin, such as a generalized allergic reaction (urticarial rash, bronchospasm, angioedema, hypotension, etc.); requirement for prohibited concomitant medications; completion of treatment/intervention as defined by the protocol; or clinical reasons believed by the physician to be life-threatening.

The daily symptom diary will include prompts to aid caregivers to remember the three daily doses of study medication. The RAs will also encourage optimal adherence to medication administration at baseline and at each of the two scheduled follow-up phone communications.

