The participant will return to the hospital at day 14–21 for the measurement of the primary outcome and to deliver the study diaries. At this visit, the RA will verify whether the participant developed new fever or required additional antimicrobials, and will have a physician or nurse perform a brief physical examination (temperature, respiratory rate, and assessment of increased work of breathing). The medication bottles will be returned and the volume of remaining medication determined. The RA will phone the caregiver one month after enrolment to verify continued clinical stability. All attempts will be made to follow up participants, even those who are already known to represent clinical failure (e.g. do not defervesce by day 4 post-recruitment and receive 10 days of open-label amoxicillin) or who receive additional interventions outside of the study (e.g. have additional antimicrobial agents prescribed by other clinicians) to ensure completeness of data collection (Fig. 1).

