All serious AEs (SAEs) that are both unexpected and related to the study product will be reported to Health Canada, and those related to the study product or procedures will be reported to the appropriate REB as soon as possible if required by the REB, but no later than 15 calendar days (7 days if fatal or life-threatening) after first knowledge of the event. Further information and significant new information on ongoing reported SAEs will be provided to the sponsor, the REB and Health Canada, as applicable. Copies of all information about the SAE will be kept in the regulatory binder.

All caregivers will be asked to complete a symptom diary form each day post-randomization until the tenth post-randomization day; questions on this form will seek information on clinical features of persistent or worsening respiratory disease (e.g. fever, difficulty breathing, overall clinical status) in addition to common (e.g. diarrhoea) and serious (e.g. anaphylaxis) AEs known to be associated with amoxicillin administration. In addition, the RA will specifically ask about symptoms and signs consistent with respiratory deterioration or amoxicillin-associated AEs. This will also be done at the time of visit 1, when the participants return to be clinically evaluated at day 14–21 post-randomization.

The SAE most likely to occur is hospitalization in the first few days post-recruitment, due to worsening respiratory status. Though the majority of children with mild CAP respond well to oral antimicrobial therapy, a small percentage will worsen and require admission to hospital because of progressive oxygenation failure and/or the need for operative drainage of pleural-based collections. These SAEs would not be related to any trial procedures, as all study participants will be receiving the first-line antimicrobial agent of choice (high-dose amoxicillin) for the first 5 days post-enrolment. We note that the risk of harm to trial participants will likely be less than to non-participants, because study staff will be contacting all study participants at intervals to verify clinical stability. As detailed above, the RAs will contact all study participants once at day 3–5 post-recruitment and once at day 7–10 post-recruitment and will be actively questioned about symptoms indicative of worsening respiratory status. Furthermore, all participants that are persistently febrile at day 4 post-recruitment will complete 10 days of open-label high-dose amoxicillin.

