These analyses will be exploratory. The following sensitivity analyses are planned: (1) intention-to-treat analysis; (2) strict per-protocol analysis including only those participants who were adherent to their medications and whose radiographs were reported by a radiologist to demonstrate alveolar infiltrates; (3) per-protocol analysis stratified by whether the saliva CRP was greater than the 75th percentile; and (4) per-protocol analysis stratified by whether a virus, an atypical pathogen, or high-level *S. pneumoniae* colonization was found in the NPS. If evidence is found of effect modification or confounding related to the above parameters additional analyses will be undertaken. The results of all analyses will be reported as estimate of effect, corresponding 95% CI and associated *p* values. All *p* values will be reported to three decimal places with those less than 0.001 reported as *p* < 0.001. The criterion for statistical significance will be set at alpha = 0.05. Table 1 provides a summary of the outcomes, corresponding hypotheses, measure, and method of analysis.

**Table 1 Tab1:** Variables, measures, and methods of analysis

Variable/outcome	Hypothesis	Outcome measure	Methods of analysis
Primary			
Clinical cure (per-protocol)	Short-course (5-day) treatment with high-dose amoxicillin is non-inferior to long-course (10-day) treatment	At visit (day 14–21) composite of: 1. Defervesced on or before day 4 2. No more than 1 further fever spike until visit 3. No tachypnoea and decreased work of breathing 4. No additional antibacterials given Dichotomous	Logistic regression
Secondary, between-group comparisons			
Absenteeism (caregiver, from work)	Short-course treatment is non-inferior to long-course treatment	Daily symptom diaries: self-reported number of caregiver-days absent from work (count)	Poisson regression
Absenteeism (child, from daycare/school)	Short-course treatment is non-inferior to long-course treatment	Daily symptom diaries: reported number of child-days absent from daycare/school (count)	Poisson regression
Mild drug adverse reactions	Fewer in short-course arm than in long-course arm	Daily symptom diaries: Reported number of child-days with diarrhoea, rash, abdominal pain, yeast infection (count)	Poisson regression
Anaphylaxis and other severe drug adverse reactions	Fewer in short-course arm than in long-course arm^a^	Daily symptom diaries, SAE reports. Dichotomous	Descriptive statistics

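### The fever criterion of the primary outcome runs to the day 14–21 visit and is to be checked from the diaries, but the diary stops on day 10, leaving 36–61% of the window without a daily record

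*Protocol article*

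**What the plan says.** The Primary outcome section of the protocol article makes fever the second of three conditions for early clinical cure: no more than one spike attributable to bacterial respiratory illness, counted from day 4 through the follow-up visit at day 14 to 21. Table 1, in the Analysis section, restates it as "No more than 1 further fever spike until visit".

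On measurement, the Primary outcome section says "Lack of fever at home will be verified through assessment of the symptom diaries". On the visit day a blinded physician or nurse "will assess temperature, respiratory rate, and evident increased work of breathing, in person using standardized protocols".

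The Follow up section introduces the diary without an end date: "The caregiver will be given a study diary to complete each day". Temperature is one of its items, and the diary is handed in at the day 14–21 visit. The end date appears under Safety and adverse events: "All caregivers will be asked to complete a symptom diary form each day post-randomization until the tenth post-randomization day". That passage lists fever among the things the form asks about.

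The other contacts are also in Follow up: "The RA will phone the caregiver once at day 3–5 and once at day 7–10", and at the visit "the RA will verify whether the participant developed new fever or required additional antimicrobials". The next scheduled call comes one month after enrolment.

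**The concern.** The article fixes both the window of the fever criterion and the last day of its named data source, and the two do not match. This is not a detail left to a fuller protocol or an analysis plan.

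The criterion needs a count of spikes, judged against temperature thresholds that differ by axillary, oral and rectal measurement. The protocol explains that one spike is tolerated so that a single faulty reading does not make a failure, which presupposes individual readings. From day 11 to the visit no scheduled daily reading exists.

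The cut-off also falls at an awkward point. Days 6–10 are the first five days off amoxicillin in the 5-day arm, and the diary covers them. The first days off amoxicillin in the 10-day arm begin on day 11, just after the diary ends. Fever soon after stopping treatment is therefore recorded daily in one arm and recalled in the other. What is at stake is how completely the primary endpoint is ascertained in a comparison that turns on a few failures per arm.

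**Working it through.** **Inputs**
- Fever window: day 4 to visit day *v*, both ends included, with *v* from 14 to 21 (Primary outcome; Table 1).
- Last diary day: 10 (Safety and adverse events).
- Last scheduled call before the visit: day 7–10 (Follow up).
- In-person temperature: visit day only (Primary outcome).

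The protocol states no figure on this point, so there is none to reproduce.

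**Coverage.** Window length = *v* − 4 + 1 = *v* − 3. The diary covers days 4–10, that is 7 days. Days without a diary = *v* − 10.

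| Visit day | Window (days) | With diary | Without diary | Share without |
|---|---|---|---|---|
| 14 | 11 | 7 | 4 | 4/11 = 36.4% |
| 21 | 18 | 7 | 11 | 11/18 = 61.1% |

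**Alternative counts.** If the visit-day temperature counts as a record, the gap is 3/11 = 27.3% to 10/18 = 55.6%. Numbering enrolment as day 1, so that the tenth post-randomization day is day 11, gives the same range. Both together give 2/11 = 18.2% to 9/18 = 50.0%. A gap remains under every reading.

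**Which failures can be hidden.** A missed failure must fail on fever alone, with its second spike after day 10. Failure to defervesce by day 4 lies inside the diary period. Tachypnoea and unresolved breathing difficulty are assessed at the visit. Additional antibacterials and admission for lower respiratory illness have their own criterion, which the Primary outcome section runs for two weeks after enrolment. Fever with another identifiable cause is not a failure. The share of days uncovered is therefore not the share of failures missed.

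**Illustration of direction only; the miss rates are assumptions with no basis in the documents.** Take 135 per arm and true failure of 12.5% (5-day) versus 5% (10-day), so that the true difference equals the 7.5-point margin. Declare non-inferiority when the upper bound of the simple (Wald) interval, 97.5% one-sided, is below 7.5 points. Exact enumeration of both binomials gives the chance of a false declaration:

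| Share of all failures missed | Missed equally in both arms | Missed in 10-day arm only |
|---|---|---|
| 0% | 3.3% | 3.3% |
| 2% | 3.6% | 3.1% |
| 5% | 4.2% | 2.8% |
| 10% | 5.4% | 2.4% |
| 25% | 11.6% | 1.4% |

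Equal misses raise the error; misses confined to the 10-day arm lower it. Nothing in the protocol says which row or column applies.

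**The case against.** The best defence is that a missing daily record is not missing information. The research assistant asks about new fever at the visit, temperature is measured that day, caregivers are taught to take temperatures, and they are asked to make contact if fever or other signs of recrudescence appear. For a day-14 visit the recall period is at most four days. The calendar is the same in both arms and the assessor is blinded. The day-10 limit also appears only once, in the safety section of a condensed article, and the full protocol (v5.0) is not shown, so the diary in use may run longer.

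Much of this stands. A reader might infer that fever after day 10 goes unascertained; the documents do not support that. A reader might also infer that the gap inflates false non-inferiority to some particular figure, such as the 5.4% or 11.6% in the table. Those values rest on assumed shares of all failures missed, while the gap exposes only late failures on fever alone, and the difference between arms in off-drug recording pulls the other way.

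The mismatch itself remains. The safety wording is explicit and names fever, and neither the undated description of the diary nor its return at the visit extends it. One question asked after up to 11 days is a poor substitute for a count of readings.

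**Conclusion.** The concern holds as an internal inconsistency affecting one component of the primary outcome. The named source for fever at home covers 7 days of an 11- to 18-day window, leaving 36–61% without a daily record, or 27–56% if the visit-day temperature counts. This takes the safety section's day-10 limit at face value and counts days from enrolment with both ends included.

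The effect on the treatment comparison cannot be derived from the documents. Only failures defined solely by repeated fever after day 10 are exposed, and how many to expect is not stated. The direction is uncertain: equal under-recording in both arms favours non-inferiority, while under-recording mainly in the 10-day arm works against it. This should be fixed because the remedy is cheap and the endpoint is primary, but it does not show that the trial's conclusion would be wrong.

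**What to change.** Extend the daily temperature line of the diary, with route of measurement, to the day of the day 14–21 visit. Amend the diary sentence under Safety and adverse events to agree with the window and data source given under Primary outcome. If the diary in use already runs to the visit, correcting that sentence is enough.

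Recruitment has been under way since August 2016. For children already enrolled, flag fever data after day 10 as recalled so that their source is visible in the dataset and the report.

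A sensitivity analysis that counts fever only through day 10 is not advised. It would keep the 5-day arm's first off-drug days and drop all of the 10-day arm's, building in the imbalance described above.

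Cost: a diary reprint, a minor amendment, and 4–11 more days of one diary line per child. The diary is already collected at that visit, so no new contact is needed.

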### Statistical analysis

#### Sample size

We estimate the baseline failure rate of standard therapy to be ~ 5%; this estimate is consistent with previous studies in children [13], is less than in similar adult studies [7], and is the approximate rate that was seen in the pilot study. We will use a non-inferiority margin of an additional 7.5%. As this is a non-inferiority trial, the crucial statistical comparison will be between the 97.5% (one-sided) CI of the difference between the failure rate of the experimental arm and the standard therapy arm; should the upper bound of this difference be smaller than 7.5%, a conclusion of non-inferiority will be reached. As the maximum baseline failure rate in the reference arm is probably 5%, the maximum failure rate in the experimental arm that would still be felt to be “non-inferior” would be 12.5%; the margin of 7.5% was selected to make the maximum failure rate in the experimental arm less than 13.5%, the median acceptable failure rate in the treatment of CAP identified in a survey of infectious-disease physicians [37]. Setting α at 5%, with 80% power, 135 participants in each arm will be required for this trial (PASS software package, NCSS LLC, Kayesville, UT, USA); as we will have accrued ~ 60 subjects in the pilot to be “rolled over”, an additional 210 participants will be required. Our experience conducting the pilot, combined with an analysis of visits to the EDs of the study sites, leads us to believe that this target should be achievable. It is estimated that the target sample size should be attainable after 2 years of enrolment.

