**Methods:**

The objective of this multicentre, randomized, non-inferiority, controlled trial is to investigate whether 5 days of high-dose amoxicillin is associated with lower rates of clinical cure 14–21 days later as compared to 10 days of high-dose amoxicillin, the reference standard. Recruitment and enrolment will occur in the emergency departments of McMaster Children’s Hospital and the Children’s Hospital of Eastern Ontario. All children in the study will receive 5 days of amoxicillin after which point they will receive either 5 days of a different formulation of amoxicillin or a placebo. Assuming a clinical failure rate of 5% in the reference arm, a non-inferiority margin of 7.5%, one-sided alpha set at 0.025 and power of 0.80, 270 participants will be required. Participants from a previous feasibility study (n = 60) will be rolled over into the current study. We will be performing multiplex respiratory virus molecular testing, quantification of nasopharyngeal pneumococcal genomic loads, salivary inflammatory marker testing, and faecal microbiome profiling on participants.

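### At 135 per arm and 5% failure, the stated one-sided 2.5% error and 80% power cannot both hold: the simple Wald bound gives 81.5% power at 3.25% error, and bounds that hold about 2.5% give about 74% power

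*Protocol article*

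**What the plan says.** The abstract (Methods) gives the design figures for a 5% reference failure rate and a 7.5% margin as "one-sided alpha set at 0.025 and power of 0.80, 270 participants will be required". The Sample size section gives the same size per arm: "Setting α at 5%, with 80% power, 135 participants in each arm will be required for this trial". The sidedness of that 5% is not stated. It agrees with the abstract if read as two-sided 5%, which is one-sided 2.5%.

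The same section fixes the scale and level of the decision: "the crucial statistical comparison will be between the 97.5% (one-sided) CI of the difference between the failure rate of the experimental arm" and the standard-therapy arm. The rule follows: "should the upper bound of this difference be smaller than 7.5%, a conclusion of non-inferiority will be reached". No method is named for computing the bound. The principal analysis is per-protocol (Analysis section), and Table 1 lists logistic regression for the primary outcome.

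**The concern.** Error rate, power, sample size, margin, event rate and decision rule are all stated, so they can be tested against one another. At 5% failure, 135 × 0.05 = 6.75 failures are expected per arm. With so few events the large-sample formula behind the sample size is unreliable, and the interval built on the same approximation tends to be too narrow on the side that matters.

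The stake is the trial's main conclusion. If the simple interval is used, a 5-day course that is truly 7.5 points worse is declared non-inferior more often than the plan says. If a better-behaved interval is used, the chance of a correct positive answer is lower than the plan says. The choice can also change the verdict on tables close to the expected one.

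**Working it through.** **Inputs.** One-sided alpha 0.025 and power 0.80 (abstract). Reference failure 5%, margin 7.5 points, 135 per arm, and an upper one-sided 97.5% bound below 7.5% (Sample size section). Two assumptions are added: true failure is 5% in both arms when computing power, which reproduces the stated size, and all 135 per arm are evaluable.

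**1. Reproduce the plan's figure.** The unpooled normal formula is

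n = (z₁₋α + z₁₋β)² × 2p(1 − p) / margin² = (1.96 + 0.8416)² × 2 × 0.05 × 0.95 / 0.075² = 132.6, so 133 per arm.

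At 135 per arm the same approximation gives Φ(0.075 / √(2 × 0.05 × 0.95 / 135) − 1.96) = 80.7% power. One-sided 5% would need only 105 per arm, so the plan's 5% must mean one-sided 2.5%. The stated 135 is therefore a normal large-sample result, not a slip. The Farrington-Manning formula, which uses the variance restricted to the null, would give 163 per arm and about 71.6% power at 135.

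**2. Enumerate the rule exactly.** Each arm's failures follow a Binomial(135, p) distribution. For all 136 × 136 possible tables, mark those where the upper bound is below 0.075 and add their probabilities. Power is taken at 5% versus 5%. False non-inferiority is taken at 12.5% (5 days) versus 5% (10 days).

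| Bound | Power | False non-inferiority |
|---|---|---|
| Wald | 81.5% | 3.25% |
| Agresti-Caffo | 77.8% | 2.69% |
| Likelihood-ratio | 77.4% | 2.69% |
| Newcombe | 74.4% | 2.49% |
| Farrington-Manning / Miettinen-Nurminen score | 74.1% | 2.23% |
| Wald, continuity-corrected | 71.6% | 1.77% |

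No row has at least 80% power with at most 2.5% error. The Wald error depends on the control rate: 4.45% at a 2% control rate and 2.97% at 8%.

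**3. Could another choice of test rescue the pair?** Raising the Wald critical value until the error is at most 2.5% at the 5% control rate alone leaves 77.6% power. A linear program over all tests with error at most 2.5% at every control rate from 0 to about 20% gives a maximum power of 75.7%.

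**4. Does the verdict change on realistic tables?** Take 7 failures in the 10-day arm and 9 in the 5-day arm. The difference is 9/135 − 7/135 = 0.0148.

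- Wald: the standard error is √(0.0667 × 0.9333/135 + 0.0519 × 0.9481/135) = 0.0287. The upper bound is 0.0148 + 1.96 × 0.0287 = 0.0711, so the table passes.
- Newcombe: the Wilson upper limit for 9/135 is 0.1219 and the Wilson lower limit for 7/135 is 0.0253. The upper bound is 0.0148 + √[(0.1219 − 0.0667)² + (0.0519 − 0.0253)²] = 0.0760, so the table fails.

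With 7 control failures, Wald passes up to 9 failures on 5 days, and the score and Newcombe bounds pass up to 8.

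**5. Size needed for 80%.** Exact power first reaches 80% and stays there (checked up to 184 per arm) at 155 evaluable per arm for Newcombe and 156 for the score bounds. That is 310 to 312 in total, against 270. At 155 per arm, score power is 79.3% and Newcombe 80.7%.

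**The case against.** The strongest objection is that 5% is a point value the plan itself treats loosely. The Sample size section calls it approximate and then describes it as probably the maximum for the reference arm. At 4% failure in both arms, score and Newcombe power at 135 per arm is about 81%, with error of 2.2% and 2.4%. At 3% power is 88%. That is correct and should be said. It does not clear the stated claim, because the plan computes its 80% at 5%. Lower control rates are also where a Wald bound exceeds 2.5% most.

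A second objection is that naming the interval belongs to the analysis plan, and that the protocol article never mentions a Wald bound. An unnamed interval alone would indeed be no fault. Here, however, no interval named later can deliver both figures at 5% failure.

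Third, 135 is what the conventional formula gives, so nothing was miscalculated. That stands. The fault lies in the properties claimed for the design.

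Fourth, the effect is moderate. Agresti-Caffo and likelihood-ratio bounds lose only 2 to 3 points of power, with error slightly above 2.5%. Newcombe itself reaches 2.6% at an 8% control rate. The verdict differs by one child for some control counts and not for others: with 6 or 9 control failures, Wald, score and Newcombe have the same cut-offs (8 and 10). All of this stands and limits the weight of the point.

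**Conclusion.** The stated pair is wrong as written. With 135 evaluable per arm and 5% failure in both arms, the design has about 80% power only with a bound whose error is 3.25%, which is 3.25 − 2.5 = 0.75 points too high. With a bound that holds about 2.5%, power is about 74%, roughly 6 points below the stated 80%. The conclusion rests on the assumptions of equal 5% failure and no losses, and it is specific to that failure rate. At 4% failure both properties hold with a score or Newcombe bound.

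The point is separate from losses and from the logistic regression in Table 1, since it holds with all 270 children evaluable and on the risk-difference scale. Losses from the per-protocol set would lower power further. As an illustration, a loss of 5% or 10% leaves 128 or 122 per arm and gives score power of about 72% or 70%.

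**What to change.** Name the decision interval as a one-sided 97.5% upper bound for the risk difference by a score method (Miettinen-Nurminen or Farrington-Manning) or by Newcombe's method, and do so before unblinding. Restate the power along these lines: 135 evaluable per arm give about 74% power at 5% failure in both arms (about 81% at 4%), with a one-sided type I error close to 2.5%. If a Wald bound is kept, state that its actual error is about 3.3% at the design rates and higher at lower control rates.

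The cost is a sentence or two and a less favourable stated power. Conduct and sample size do not change. Keeping 80% at 5% failure would instead take about 155 to 156 evaluable per arm, but that is not asked for here.

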#### Analysis

We will use descriptive statistics to describe the baseline characteristics of the groups reported as count (percent) for categorical variables, and mean (standard deviation) or median (first quartile, third quartile) for continuous variables, depending on the distribution. We will adopt Consolidated Standards of Reporting Trials (CONSORT) criteria for reporting on non-inferiority and equivalence trials in reporting the trial [38]. The principal analysis will be per- protocol, as is recommended for non-inferiority trials [39–41]. The principal analysis is not intention-to-treat (ITT) simply because the effect of ITT analysis is to reduce the difference seen between treatment groups; in a superiority trial, ITT analysis functions to buttress a conclusion of superiority, but in a non-inferiority trial it could lead to a false conclusion of non-inferiority by masking a true difference between treatment arms.

We will use logistic regression to analyze binary outcomes, Poisson regression for count outcomes and linear regression for continuous outcomes. Descriptive analyses will be used to compare rates of viral and atypical co-infections in the entire study population and between groups.

We will perform some subgroup analyses by adding an interaction term between treatment group (5-day vs. 10-day course) and the following subgroups: (1) older (age 5–10 years) vs. younger (age <5 years); (2) higher vs. lower salivary CRP; and (3) virus/*Mycoplasma* detected in baseline NPS vs. no virus detected. These interaction tests will be exploratory in nature and not adjusted for multiple testing [42].

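### 270 is the number needed if every child is analysed, but it is also the enrolment target for a trial whose principal analysis is per-protocol, so the stated 80% power has no protection against losses

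*Protocol article*

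**What the plan says.** The Abstract (Methods) gives the design inputs: "Assuming a clinical failure rate of 5% in the reference arm, a non-inferiority margin of 7.5"%, then "one-sided alpha set at 0.025 and power of 0.80, 270 participants will be required".

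The Sample size section repeats the rate ("We estimate the baseline failure rate of standard therapy to be ~ 5"%) and the margin ("We will use a non-inferiority margin of an additional 7.5"%). It sets the decision rule: "the crucial statistical comparison will be between the 97.5% (one-sided) CI of the difference" in failure rates, with non-inferiority concluded if the upper bound lies below the margin. It then puts alpha at 5%, with no sidedness given, and says: "with 80% power, 135 participants in each arm will be required for this trial". About 60 pilot participants are carried over and 210 more are to be recruited, which makes 270 enrolled. No loss or exclusion rate is mentioned.

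The Analysis section says: "The principal analysis will be per- protocol, as is recommended for non-inferiority trials". Intention-to-treat is listed as a sensitivity analysis. A strict per-protocol set, limited to adherent children with radiologist-reported alveolar infiltrates, is a further sensitivity analysis.

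**The concern.** A power statement has to refer to the number analysed. Here one number serves as both the number required for 80% power and the number enrolled, while the conclusion rests on a set that can only be equal to or smaller than the enrolled cohort.

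The article itself describes ways in which children may leave that set or lack an outcome. The outcome needs an in-person visit at day 14–21, caregivers may withdraw before it, the experimental regimen may be stopped early, and the Discussion accepts that adherence may fall short.

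At 5% failure only about 7 failures per arm are expected (0.05 × 135 = 6.75), so precision is the main risk. If power is lower than stated, an inconclusive result could be misread as evidence against the short course.

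**Working it through.** **Inputs.** Failure rate 5% in the reference arm, margin 7.5 points, 80% power and one-sided alpha 0.025 (Abstract; Sample size); 1:1 allocation (Study interventions). Failure in the 5-day arm is taken as 5%, that is, no true difference. This is the usual assumption, but the article does not state it.

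**Step 1: reproduce the stated size.** Unpooled normal formula:

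n = (1.96 + 0.8416)² × 2 × 0.05 × 0.95 / 0.075² = 132.6, so 133 per arm.

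The stated 135 exceeds this by 2 per arm (2/135 = 1.5%). It contains no allowance for losses.

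**Step 2: the alpha wording.** With one-sided 0.05 the same formula gives 104.4, so 105 per arm, and 135 per arm would have 88% power. Thus 135 matches one-sided 0.025, the level in the Abstract and in the 97.5% one-sided bound. The 5% in the sample-size sentence is consistent only as the two-sided label for that level.

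**Step 3: power when some of the 270 are not in the per-protocol set.** Normal approximation: power = Φ(0.075 / √(2 × 0.05 × 0.95 / n) − 1.96).

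- n = 135: 0.075 / 0.02653 − 1.96 = 0.867, power 80.7%.
- n = 121: 0.075 / 0.02802 − 1.96 = 0.717, power 76.3%.

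The exact columns sum the binomial probabilities of all outcomes that meet the rule. The Wald column uses the unpooled interval, and the score column uses the Miettinen-Nurminen interval. The loss rates are assumptions.

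| Assumed loss | Per arm | Wald, normal approx. | Wald, exact | Score, exact |
|---|---|---|---|---|
| 0% | 135 | 80.7% | 81.5% | 74.1% |
| 5% | 128 | 78.6% | 79.5% | 72.4% |
| 10% | 121 | 76.3% | 75.8% | 68.2% |
| 15% | 115 | 74.2% | 75.2% | 64.1% |
| 20% | 108 | 71.5% | 74.1% | 61.2% |

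Exact power moves in steps because failures are whole numbers (Wald at 122 per arm is 77.3%), so differences of a point or so should not be over-read. Compare exact with exact: setting the normal-approximation Wald column beside the exact score column would mix two kinds of figure.

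**Step 4: sensitivity to the failure rate.** The Sample size section calls 5% the probable maximum in the reference arm. At 4% in both arms, exact Wald power is 83.7% with 10% loss and 82.4% with 20% loss, and it is 82% or more at every loss level in the table. With the score interval at 4% and 10% loss it is 74.6%.

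**The case against.** **The size is not miscalculated.** This stands: 135 reproduces. The point concerns which number the power refers to.

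**An allowance may sit in the full protocol, and an article need not give one.** Fair as to detail. But the article prints both an enrolment total and a power, and Step 1 shows that this total leaves no room for an allowance at the stated alpha. To find one inside 135, the base would have to be 105, leaving 1 − 105/135 = 22%. That base needs one-sided 5%, which the Abstract and the 97.5% bound exclude.

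**A reader might infer that the trial certainly has clearly less than 80% power.** The documents do not support this. They give no loss rate and do not define the principal per-protocol set. The adherence and radiologist restrictions belong to the strict sensitivity set, so the principal set may exclude few children. The Follow up section commits to following all participants and describes children who do not defervesce by day 4 as clinical failures, so stopping the experimental regimen need not remove a child from the analysis. At 5% loss the Wald figure falls only about 1 point short of 80%, and a true rate of 4% restores it.

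**A reader might infer that the 5% alpha makes the sample size wrong.** It does not. The level is fixed elsewhere in the article, and 135 agrees with it. Only the wording is loose.

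**A reader might infer that the planned interval exceeds the stated error rate.** At 12.5% versus 5% with 135 per arm, exact one-sided error is 3.25% for the Wald interval and 2.23% for the score interval, against 2.5%. But the article names no interval for the difference, and that choice commonly belongs to the analysis plan. These figures and the score powers are therefore conditional on the method chosen.

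**Conclusion.** The point holds in a limited form. The article uses the bare evaluable number as its enrolment target while resting its conclusion on the per-protocol set, so the stated 80% is correct only if essentially every enrolled child is analysed. On the normal approximation, losing more than two children per arm takes power below 80%.

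At 5% failure in both arms and assumed losses of 5 to 20%, exact power runs from about 80% down to 74% with a Wald interval and from 72% down to 61% with a score interval. If a score interval is used, power is about 74% even with no loss. The size of the shortfall rests on three things that the article does not settle: the share of children outside the per-protocol set, the interval method, and whether the true failure rate is 5% or lower. What is established is that the stated power is unprotected against losses, not that it will be missed by a known amount.

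**What to change.** In the Sample size section:

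- State that 135 per arm is the evaluable per-protocol number.
- Give the expected share of enrolled children outside the principal per-protocol set, and restate the power of 270 enrolled for that size and for the interval method to be used. Show it over a range of losses (the table above can serve) and note that power is higher if the failure rate is below 5%.
- As a minor wording alignment, replace the 5% alpha by one-sided alpha of 0.025 (two-sided 5%).

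The cost is a few restated figures and a less favourable stated power. No extra enrolment is required. Whether to keep 80% after losses is a separate decision for the sponsor. For scale, 135/(1 − d) gives 143, 150, 159 and 169 per arm at 5, 10, 15 and 20% loss.
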